No literature describing research combining mirror therapy and action observation could be found. Their combined use could increase the perception of the affected upper limb and facilitate motor recruitment and quality of movement, through visual illusion. In addition, with action observation, the spontaneous use and participation of the affected upper limb in daily activities through repetition of observed tasks can be increased. The combination of mirror therapy and the action observation therapy (MTAO) could facilitate the quality of movement of the upper limb, improving its structure and function and providing greater cortical activation and spontaneous use, through the repetition of specific movements. Furthermore, it can be done at home using a single intervention protocol. Conducting the therapy in the child’s home can involve the child in repeated practice of tasks and involve the family in the treatment process [29]. It has been reported that parents of children with disabilities have higher levels of stress than parents of typically developing children [30], which may suggest that the home is a viable setting for implementing therapy with parents. Their collaboration in producing target settings for treatment programs that involve family values and priorities may decrease the parents’ stress level [31]. The application of MTAO has a great clinical implication, since it is a low intensity program, which can be carried out at home with the follow up of a therapist, reducing economic costs and improving the interaction family—child—therapist.

The aim of the research will be to study the functionality of the affected upper limb in hemiplegia in children aged 6 to 12 years after applying two intervention protocols: MTAO and AOT”.

The hypotheses are: (1) “Both MTAO and AOT improve the functionality of the affected upper limb, with the effect of MTAO being greater” (2) “MTAO increases the spontaneous use and the manual ability in the affected upper limb more than AOT”. (3) “MTAO improves the muscle activity of the affected hand and increases grip strength more than AOT”.

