### 2.6. Data Analysis

Statistical analyses will be performed with SPSS v.24.0 (SPSS Inc., IBM, Chicago, IL, USA). Statistical significance will be set at *p* < 0.05. The test Shapiro-Wilk test will be used to study normality of the sample.

A descriptive analysis of demographic variables will be performed using means and standard deviation for normal distribution variables, and medians and interquartile ranges for non normal distribution variables. The categorial variables will be described using frequencies and %.

To evaluate statistically significant differences intergroup in the variables at baseline, the independent Samples T-test (normal distribution) or the Mann-Whitney U test (non normal distribution) will be used. To study the effects of the interventions on the outcomes measures at four time points, for normal distribution variables, a two-way (intervention × time) repeated measures ANOVA test will be conducted. The Bonferroni correction will be employed for pairwise post-hoc comparisons to further analyze significant interactions. The Greenhouse–Geisser adjustment will be applied to correct for the lack of sphericity (Mauchly’s sphericity test, *p* < 0.05) whenever is necessary. For non-normal distribution variables, the Friedman test will be used. Bivariate correlation coefficients will be estimated to examine the relationship between the subjects’ age, sex, or affected upper limb.

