## 3. Discussion

The aim of this research is to compare the effect of two intervention protocols (MTAO and AOT) on the functionality of the affected upper limb in infantile hemiplegia, from 6 to 12 years old.

The motor acts are usually combined to form target-related actions. The same motor acts can be included in actions with different final objectives. It has recently been shown that the visual responses of a subset of the lower parietal and premotor neuron system, studied both during observation and in the execution of grasping acts in different actions (e.g., grasping to place something or grasping to eat), are modulated by the target of the final action (placing or eating) [48,49]. Therefore, during the observation of a person performing an action, the watcher codes the final objective of the observed action (corresponding to the person’s intention) and the objective of the motor act included in that specific action. Thus, the child can internalize the intentionality of the activity observed and the motor act performed. These findings suggest that AOT will increase the spontaneous use of the affected upper limb through observation and imitation of actions, and thus encourage the child’s participation within their natural context and in daily activities. When the proposed activities are targeted at a functional goal or represent everyday activities, this automatic use is encouraged within the everyday environment. Considering the reduction of selective movements and the difficulty of executing adequate movements, mirror therapy could help to improve movement quality in dynamics and manual dexterity measured through grasping [37]. In our study, improvements in the coordination of wrist flexor and extensor contraction and more fluid manual dexterity can be obtained. Therefore, the MTAO protocol could induce changes in the spontaneous use and in the quality of movement of the affected upper limb.

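### For outcomes judged non-normal, the plan names only the Friedman test, which does not compare MTAO with AOT, so the between-arm hypotheses have no test on that branch

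*Protocol article*

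**What the plan says.** All of the analysis text is in section 2.6 of the protocol article. The route is set by a normality test: "The test Shapiro-Wilk test will be used to study normality of the sample". The article does not say which values are tested (baseline or every visit, arms pooled or separate) or how many rejections make an outcome non-normal.

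The two routes are:
- Normal: "for normal distribution variables, a two-way (intervention × time) repeated measures ANOVA test will be conducted", with Bonferroni-corrected pairwise comparisons to follow up significant interactions.
- Not normal: "For non-normal distribution variables, the Friedman test will be used". Nothing further is named.

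The only non-parametric between-group test in the section is restricted to baseline: "To evaluate statistically significant differences intergroup in the variables at baseline, the independent Samples T-test (normal distribution) or the Mann-Whitney U test".

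The Introduction states three hypotheses:
- Hypothesis 1: "Both MTAO and AOT improve the functionality of the affected upper limb, with the effect of MTAO being greater".
- Hypothesis 2: "MTAO increases the spontaneous use and the manual ability in the affected upper limb more than AOT".
- Hypothesis 3: "MTAO improves the muscle activity of the affected hand and increases grip strength more than AOT".

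The Discussion gives the aim as a comparison: "The aim of this research is to compare the effect of two intervention protocols (MTAO and AOT").

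**The concern.** The normal branch carries the intervention factor and the non-normal branch drops it. The Friedman test asks whether values differ between visits within children. It does not ask whether one randomised group changed more than the other.

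This is not a detail left to a later document. The article fixes a specific test for the branch, and that test does not answer the question the trial was randomised to answer. If the plan is followed as written, an outcome on this branch yields either one pooled p-value for time or two p-values, one per arm. Neither estimates or tests the MTAO-AOT difference. A pooled time effect, or significance in one arm only, could then be mistaken for evidence about superiority.

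**Working it through.** **1. Which claims need a between-arm test**

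| Claim | Type | Test if normal | Test if non-normal |
|---|---|---|---|
| H1, first half: both arms improve | within arm | time effects in the ANOVA | Friedman run in each arm could serve |
| H1, second half: MTAO effect greater | between arms | intervention × time | none |
| H2: spontaneous use, manual ability | between arms | intervention × time | none |
| H3: muscle activity, grip strength | between arms | intervention × time | none |

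**2. The plan's own figure is for a two-group comparison**

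Inputs from section 2.2: effect size 1.40, 80% power. Two-sided alpha 0.05 is taken from section 2.6; the 0.05% printed in section 2.2 does not reproduce the stated size, and sidedness is not stated.

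Normal approximation: n = 2(1.960 + 0.842)² / 1.40² = 2 × 7.85 / 1.96 = 8.01, rounded up to 9 per group. The exact t-test gives 9.08, rounded up to 10, with 84% power at 10. The stated 10 per group is reproduced, and it is sized for MTAO against AOT on the AHA.

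**3. What the Friedman statistic contains**

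Q = [12 / (N k (k+1))] Σ R_j² − 3N(k+1), where k = 4 visits, N is the number of children and R_j is the sum over children of the within-child ranks at visit j. Arm does not appear. With both arms pooled (N = 20), shuffling the arm labels among the children leaves every R_j, and so Q, unchanged. Run in each arm (N = 10), it gives two separate tests of change over time and no test of their difference.

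**4. How often a truly normal outcome would enter this branch**

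Assumptions: 10 per arm, four visits, multivariate normal data, visit correlation 0.5-0.9, Shapiro-Wilk at 0.05, and any single rejection counts as non-normal. If the m tests were independent the chance would be 1 − 0.95^m. Correlation between visits lowers it.

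| Rule (none is stated) | m | 1 − 0.95^m | Simulated |
|---|---|---|---|
| Baseline only, arms pooled | 1 | 5.0% | about 5% |
| Baseline, each arm | 2 | 9.8% | about 10% |
| Any of four visits, arms pooled | 4 | 18.5% | 13-19% |
| Any of eight arm-by-visit cells | 8 | 33.7% | 27-34% |

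**5. What the branch reports when the arms do not differ**

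Assumptions, not document values: the same gain in both arms at all three post-baseline visits, normal data, correlation 0.7, 10 per arm. Over gains of 0.3 to 0.7 SD, pooled Friedman is significant in about 28-95% of trials. Separate tests are significant for MTAO but not AOT in about 11-25%. The second range has a simple source: if each arm's test is significant with probability p, MTAO only occurs with probability p(1 − p), which peaks at 0.25 when p = 0.5.

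A second set used skewed data (lognormal, log-scale SD 0.8, correlation 0.6, 4,000 runs, 10 per arm). It compares Friedman with Mann-Whitney on change from baseline to week 4. Shifts are in SD of the log values.

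| Shift MTAO, AOT | Pooled Friedman | Per arm: MTAO only | Mann-Whitney on change |
|---|---|---|---|
| 0.8, 0.8 (no difference) | 94.0% | 22.9% | 4.5% |
| 1.4, 0 | 58.8% | 94.7% | 90.8% |
| 0.7, −0.7 | 2.3% | 24.8% | 82.2% |

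In the first row the per-arm rejection rates were 63.7% and 64.4%, and 0.637 × (1 − 0.644) = 22.7%, in line with the 22.9% simulated. Pooled Friedman rejects most often where the arms do not differ and almost never where they move in opposite directions.

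**6. Whether a rank test fits the planned size**

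Dividing the t-test n by the relative efficiency of Mann-Whitney gives 9.08 / 0.955 = 9.5 (normal data) to 9.08 / 0.864 = 10.5 (worst case), that is 10 to 11 per group. The plan's 10 plus 20% is 12. This is for one comparison at 0.05. With Bonferroni over three visits, alpha is 0.05 / 3 = 0.0167, the exact t-test n becomes 12.2, and the same division gives 12.8 to 14.1, or 13 to 15 per group for 80% power at any one visit.

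**The case against.** A reader might infer that the trial's hypotheses as a whole go untested. The documents do not support that. The first half of hypothesis 1 is a within-arm statement that a Friedman test in each arm can address, and outcomes judged normal keep a valid between-arm term in the ANOVA.

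A reader might also infer that the AHA is likely to lose its between-arm test. That depends on a rule the article does not give. If normality is judged once at baseline with arms pooled, a truly normal AHA is diverted only about 5% of the time. Section 2.5.1 describes the AHA as a Rasch-based interval measure, so the ANOVA route is plausible for it. Nor does the article show that JTHFT times or EMG amplitudes are skewed; that would be an outside expectation.

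The percentages in step 5 rest on chosen gains, correlations and distributions. The plan does not commit to reading significance in one arm only as superiority, so those figures show a risk and do not predict what will be reported. The study is also called a pilot.

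All of this limits the scope, and none of it supplies the missing test. No other section names a between-arm analysis for non-normal outcomes, and a pilot that states superiority hypotheses still needs a test that addresses them. A further temptation is to conclude that the ANOVA must give way to a mixed model for every outcome. The defect does not require that, because the intervention-by-time term already compares the arms on the normal branch.

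**Conclusion.** The concern holds in this form: for every outcome judged non-normal, the test named in section 2.6 cannot assess MTAO against AOT, so hypotheses 2 and 3 and the second half of hypothesis 1 have no planned test there. This follows from the text and from the form of the Friedman statistic, and needs no simulation.

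How often it will matter is uncertain. For a truly normal outcome it ranges from about 5% to 34%, according to how Shapiro-Wilk is applied. The false signals of about 28-95% (pooled) and 11-25% (MTAO only) with equal arms are illustrations that assume gains of 0.3 to 0.7 SD and visit correlation 0.7. Because the AHA can fall into the branch, the randomised comparison on the main outcome is exposed, and the text should be corrected before outcome data are seen.

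**What to change.** In section 2.6, replace Friedman as the test of the intervention effect for non-normal outcomes with one prespecified between-arm test. Mann-Whitney on change from baseline at week 4, 3 months and 6 months would serve, as would a permutation test of the same differences. Choose one of these and apply the Bonferroni correction that the plan already uses for its post-hoc comparisons. Keep Friedman, if wanted, only as a within-arm description, and state that superiority will not be inferred from significance in one arm alone. State also which values Shapiro-Wilk is applied to and what result sends an outcome to this branch.

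Replacing the repeated measures ANOVA with a mixed model for all outcomes is optional and not needed to correct this error.

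The cost is analysis wording: no extra children, visits or measurements. There is one trade-off to settle in the text. A single comparison at 0.05 fits within 12 per group, whereas Bonferroni over three visits needs about 13 to 15 per group for 80% power at a given visit. The plan should therefore either accept somewhat lower power per visit or name one visit as the main comparison.

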### 2.7. Ethical Aspects

The study was approved (Reference N: 420-20-24) by the CEU-San Pablo university Ethics Committee and will be conducted in accordance to the World Medical Association Declaration of Helsinki. The current Spanish data protection law will be complied with. Before the study began, the consent of the families and children’s caregivers will be provided. The data collected will be used exclusively for this research and anonymisation will be carried out. To ensure the confidentiality and privacy of the data, a numerical code will be assigned to each participant. The outcome measures will be associated with the numerical codes, and not with the personal data of the participants. The identifying list of the numerical codes will be kept by the principal researcher, using a password-protected file. The data of the outcome measures will therefore be anonymised. The principal researcher will be the only person to have access to the entire set of data, which will be kept in password-protected files. In both cases, they will be stored on computers protected by a security password. Under no circumstances will personal information be divulged.

## 3. Discussion

The aim of this research is to compare the effect of two intervention protocols (MTAO and AOT) on the functionality of the affected upper limb in infantile hemiplegia, from 6 to 12 years old.

The motor acts are usually combined to form target-related actions. The same motor acts can be included in actions with different final objectives. It has recently been shown that the visual responses of a subset of the lower parietal and premotor neuron system, studied both during observation and in the execution of grasping acts in different actions (e.g., grasping to place something or grasping to eat), are modulated by the target of the final action (placing or eating) [48,49]. Therefore, during the observation of a person performing an action, the watcher codes the final objective of the observed action (corresponding to the person’s intention) and the objective of the motor act included in that specific action. Thus, the child can internalize the intentionality of the activity observed and the motor act performed. These findings suggest that AOT will increase the spontaneous use of the affected upper limb through observation and imitation of actions, and thus encourage the child’s participation within their natural context and in daily activities. When the proposed activities are targeted at a functional goal or represent everyday activities, this automatic use is encouraged within the everyday environment. Considering the reduction of selective movements and the difficulty of executing adequate movements, mirror therapy could help to improve movement quality in dynamics and manual dexterity measured through grasping [37]. In our study, improvements in the coordination of wrist flexor and extensor contraction and more fluid manual dexterity can be obtained. Therefore, the MTAO protocol could induce changes in the spontaneous use and in the quality of movement of the affected upper limb.

This research has some limitations. Firstly, the lack of cross-cultural validation in Spanish of some of the measurement tools used, such as the AHA. In addition, a group with conventional intervention has not been included. As strengths, it highlights that it is the first research to evaluate the effect of mirror therapy combined with action observation therapy on upper limb functionality. In addition, the intervention protocols will be carried out at home, which means reducing economic costs and optimizing family resources. Finally, the results will improve clinical practice.

The results of our randomized controlled trial will be disseminated to the scientific community through scientific (peer-reviewed) journals and congress. In addition, research results will be presented to stakeholders, including patients, families and physicians.

## 4. Conclusions

The study of functional changes in the affected upper extremity in children with hemiplegia after the use of AOT or MTAO will help clinicians in the design and selection of appropriate therapeutic strategies to improve the functionality of the affected upper extremity. In addition, this will allow the home-based implementation of the interventions with the involvement of the family.

## Figures and Tables

**Figure 1 ijerph-18-01051-f001:**
[figure not shown]
Recruitment, assessment and follow-up.

**Table 1 ijerph-18-01051-t001:** Activities for Action Observation therapy.

**Unimanual activities**	Remove the lid from a container, remove marbles and place them in a glass. Pour water into a glass. Take a colored card, turn it over and place it with a similar figure to make pairs. Use a stamp, making figures in a horizontal plane, that is, on a paper on the table. Take coins from the table, put them in a slotted container. Take a sponge and dip it in finger paint, and then squeeze the foam in a horizontal plane, on the table. Lift the open lid of a tube containing colored paint and squish it to throw the paint onto a sheet of paper and spread it out. Use a toy fishing rod and catch magnetic animals or just catch magnetic animals.
**Bimanual Activities**	Chop up tissue paper. Wet a small towel and drain it. Stick cards on your sign on the table on a horizontal plane and/or on felt paper on a vertical plane. Make a large ball of clay and roll it with both hands until it is thrown at the end of the table. Open a coin box and take out 5 coins and put them back in and close the coin box. Build figures with Lego pieces. Apply glue stick on a piece of paper and throw the pieces of tissue paper cut earlier with both hands and glue them to create a picture.

**Table 2 ijerph-18-01051-t002:** Activities for mirror therapy into MTAO group.

**Activities**	Touch with the tips of the fingers a plasticine base for 2 min (Rest 30 s) The movement of the fingers is worked; the thumb touches each one of the fingertips for 2 min. (Rest 30 s) We work the thumb and index finger clamp with the contact of both fingers putting a resistance through a rubber between thumb and index finger for 2 min. (Rest 30 s) We will place a sponge in each of the hands to work the global grip. Squeeze and release the object and therefore also the grip strength for 2 min. (Rest 30 s) Extension movement of both wrists on a plasticine base for 2 min. (Rest 30 s) Prono-supination of the forearm, starting from a pronation position for 2 min. (Rest 30 s before starting TOA)
